## Methods/design

### Trial design

The Redyor study is a prospective randomized single-blind clinical trial aimed to determine the benefits of early rehabilitation to preserve swallow function and quality of life in patients with HNC receiving radiotherapy, following the Standard Protocol Items: Recommendations for Interventional Trials (SPIRIT) [31]. Throughout the recruitment period, patients who provide their informed consent (Additional file 1) to participate will be randomized to one of two groups: early intervention or post-CRT intervention. No major changes to methods after the start of the study are planned. This trial has been approved by the local Clinical Ethics Committee (Additional file 2).

### Settings and locations

Recruitment will be carried out in the Radiotherapy Department at the Parc de Salut Mar (Hospital del Mar and Hospital de l’Esperança), Barcelona, Catalonia, Spain. Baseline dysphagia assessments will be performed in the Swallowing Disorders Unit of the Physical Medicine and Rehabilitation Department at Hospital de l’Esperança and all VFSS assessments will be conducted in collaboration with a radiologist. Statistical analysis will be done at the Hospital del Mar, in the Medical Research Institute (IMIM). Study sites and phases are summarized in the flow diagram (Fig. 1).

**Fig. 1 Fig1:**
[figure not shown]
The Redyor study flow diagram

### Eligibility criteria

Patients with advanced HNC receiving radiotherapy will be eligible to participate in this clinical trial. Potential participants will be excluded if they have previous history of HNC and/or head or neck radiation therapy or surgical treatment, or of dysphagia due to causes other than cancer. Inclusion and exclusion criteria are listed in Table 1. During the study period, a patient will be excluded from the study if any of the following occurs: emergence of any of the exclusion criteria, onset of any disease or medical condition that will make it difficult for the patient to continue participation, decision to withdraw from the study for any reason, transfer out of the service area or death, impossibility to practice exercises due to medical condition.

**Table 1 Tab1:** Inclusion and exclusion criteria of ReDyOr study

Inclusion Criteria	Exclusion criteria
Advanced HNC	Previous history of HNC
Receiving Radiotherapy	Previous head or neck radiation therapy
	Surgical treatment on HNC area
	dysphagia due to causes other than cancer

*HNC* Head and neck cancer

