### Intervention

The training protocol consists of IEMT and standard swallowing exercises. Patients will be instructed to maintain a rate of 15–20 breaths/min using the Orygen-Dual® valve (described elsewhere in detail) [21, 22], a respiratory device that allows patients to train inspiratory and expiratory muscles simultaneously. Training loads will be set at a pressure equivalent to 10 maximal repetitions (if tolerated). These external pressures will be regulated weekly at 30% of maximal inspiration/expiration respiratory measures obtained. Patients will be instructed to perform 3 sets of 5 repetitions and standard swallowing exercises (mobility and tonicity exercises of the tongue, palate, larynx, and constrictor muscles), 3 times/day, 5 days/week, for 21 weeks. An experienced swallowing therapist will supervise IEMT weekly. The protocol will be the same for both groups, but one group will start 2 weeks before CRT and the other one will begin immediately after completing CRT (Fig. 1).

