### Strengths and limitations of the study

The study has several potential limitations that must be considered. First, losses to follow-up are common in cancer studies; to address this concern, sample size estimation assumed a loss of about 20% of patients (higher than the usual 10–15% used in previous studies). We presume that these losses will affect both study arms equally. Second, the study lacks a control group; however, this design is justified by the available evidence of the benefits of swallow and speech therapy in patients with HNC-related dysphagia.

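### Randomised patients are removed from the study, not only from the exercise programme, for events plausibly tied to swallowing, and the presumption of equal losses by arm is unsupported

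*Protocol article*

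**What the plan says.** The Eligibility criteria section lists events after which, during the study period, a patient leaves the study: "a patient will be excluded from the study if any of the following occurs: emergence of any of the exclusion criteria", then "onset of any disease or medical condition that will make it difficult for the patient to continue participation", then withdrawal, transfer out of the area or death, and finally "impossibility to practice exercises due to medical condition". The wording concerns the study, not the exercise programme. Nothing in the article says that a removed patient is still assessed, or is analysed in the assigned group.

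Of the exclusion criteria in Table 1, prior head and neck cancer (HNC) and prior radiotherapy are history items that can hardly arise later. "Surgical treatment on HNC area" can.

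The Intervention section gives both arms the same programme, "3 times/day, 5 days/week, for 21 weeks", but "one group will start 2 weeks before CRT and the other one will begin immediately after completing CRT".

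Statistical methods says that reasons for non-adherence are recorded and that missing data are dropped. It plans t-tests first and mixed models later. On attrition, the Strengths and limitations section says: "We presume that these losses will affect both study arms equally". The section on the study's repercussions remarks that many HNC patients are lost to follow-up because of CRT toxicity.

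**The concern.** A randomised comparison is protected only while patients stay in the group they were assigned to, whatever happens to them afterwards. Here, events after randomisation end membership. Medical inability to do tongue, laryngeal and respiratory exercises, intercurrent illness and surgery in the HNC area are all plausibly linked to how well the patient swallows, and the primary outcome is change in PAS on videofluoroscopy. The Background itself ties CRT to swallowing disturbance, malnourishment and aspiration.

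The trial compares two timings of one programme, and exposure to one of the removal rules depends on that timing. If removal depends on both arm and swallowing status, the analysis compares patients who were able to train, not the two randomised strategies. An analysis plan that is not shown could define an as-randomised population, but it could not recover assessments that were never made because the patient had been taken off study.

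**Working it through.** **1. The plan's own figure.** Inputs from Sample size calculation: PAS difference 2, SD 2.3, two-sided alpha 0.05, power 0.80.

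n per arm = 2 × [2.3 × (1.960 + 0.842) / 2]² = 20.76, so 21. Adding 5 gives 26 per arm and 52 in total. The stated size reproduces. (Dividing by 0.8 instead would give 27 per arm, a difference of 2 patients overall.) The allowance for loss protects precision only.

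**2. Exercise windows, from the Intervention section.**

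| Arm | Starts | Window of 21 weeks |
|---|---|---|
| Early | 2 weeks before CRT | 2 weeks before CRT, then 21 − 2 = 19 weeks from its start |
| Late | end of CRT | entirely after CRT |

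The inability-to-exercise rule can therefore act through CRT in the early arm, and mainly after CRT in the late arm. The general-illness rule can act during CRT in both.

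**3. Illustrative bias.** The document gives no removal rates by arm and no link between removal and PAS, so both are assumed. Treat the PAS change as normal with SD 2.3, and remove the worst fraction q on a severity score that correlates rho with it. The mean of the retained patients falls by

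shift(q) = rho × 2.3 × φ(z₁₋q) / (1 − q).

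With rho = 1:
- q = 0.10: 0.45
- q = 0.20: 2.3 × 0.280 / 0.8 = 0.805
- q = 0.30: 1.14

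Bias in the between-arm difference, in PAS units (the sign depends on which arm loses more):

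| Removal by arm | rho 0.3 | rho 0.5 | rho 0.7 | rho 1 |
|---|---|---|---|---|
| 20% / 20% | 0 | 0 | 0 | 0 |
| 15% / 25% | 0.10 | 0.17 | 0.24 | 0.34 |
| 10% / 30% | 0.21 | 0.35 | 0.49 | 0.69 |

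The extreme case is 20% removed as the worst in one arm and 20% at random in the other. It gives 0.805 units, or 0.805 / 2 = 40% of the target, and 0.40 units at rho 0.5.

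**4. Effect on the test.** Simulation with 26 randomised per arm, 6,000 runs, and a t-test on those retained:

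| Removal early / late | rho | Type I error | Power, true difference 2 | Mean estimated benefit |
|---|---|---|---|---|
| 20% / 20% | 0.5 | 0.053 | 0.82 | 2.00 |
| 20% / 20% | 0.7 | 0.050 | 0.86 | 1.99 |
| 10% / 30% | 0.5 | 0.070 | 0.65 | 1.64 |
| 10% / 30% | 0.7 | 0.118 | 0.64 | 1.52 |
| 30% / 10% | 0.5 | 0.078 | 0.91 | 2.34 |
| 30% / 10% | 0.7 | 0.114 | 0.96 | 2.48 |

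In every row, average loss is the planned 20%, so meeting that allowance says nothing about bias.

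**5. Retaining patients.** By the normal approximation, power is 0.88 with all 26 per arm and 0.80 with 21. The first is an upper limit, because some retained patients will lack videofluoroscopy.

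**The case against.** The strongest case on the other side is that the text establishes a removal rule but not a bias. Four stronger readings are tempting, and the document does not support them.

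- **The design contradicts equal losses.** The schedule shows different timing, not different numbers or severity. The illness clause acts in both arms during CRT, and a late-arm patient who finishes CRT unfit to train could be removed at that point. Equal loss is unsupported, not refuted.
- **The worst swallowers are dropped.** The rule speaks of medical conditions, not of PAS. The link to swallowing is a plausible inference from the Background and the remark on CRT toxicity. It is not stated.
- **Radiation-induced dysphagia would itself trigger removal**, through "dysphagia due to causes other than cancer". The narrative treats this as history before entry, and dysphagia after CRT is what the trial measures, so the reading is strained.
- **The bias is 0.80 units.** That figure needs perfect selection on PAS in one arm and random removal in the other, under one common rule.

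It is also fair that reasons for non-adherence are recorded, that missed sessions prompt a telephone call, and that the planned mixed models can use visits before removal. The analysis population may be defined in a plan not shown. These points soften the concern but do not answer it. The article itself takes patients off study and drops missing data, so this is more than silence.

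Finally, Trial status puts the end of data collection at 29 April or May 2019, before publication on 14 August 2019. Extra visits may no longer be possible.

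**Conclusion.** The point holds in this form: the protocol does not separate stopping the exercises from leaving the study, the removal events are plausibly related to the primary outcome, and the statement on equal losses has no support. Followed as written, the plan gives a comparison of selected patients. The size and direction of bias cannot be derived from the document. With assumed removal of the worst 10% versus 30%, bias is about 0.2 to 0.7 PAS units, or roughly 10% to 35% of the 2-unit target. With like selection at 20% in each arm it is about zero. These figures assume a normally distributed change with SD 2.3 and removal ranked on a correlated severity score. A larger loss in the early arm would flatter early intervention, and a larger loss in the late arm would hide a benefit.

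**What to change.** - **Separate stopping the exercises from leaving the study.** When a patient should stop exercising is a clinical matter and is not addressed here.
- **Follow-up.** Except for withdrawal of consent, death, or a transfer that makes assessment impossible, keep patients on the scheduled assessments where visits remain. Otherwise, retrieve and use every assessment already recorded.
- **Analysis.** Analyse all randomised patients in their assigned group, using the planned mixed model on all available visits in place of discarding patients with missing data. Add a sensitivity analysis for data not missing at random. Any analysis of programme completers is secondary.
- **Reporting.** Give removals and their reasons by arm and visit, and delete the equal-loss presumption.

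The sample size does not change. The cost is a clarification of the text, some data retrieval and one further analysis, plus visits already scheduled if any remain. The downside is small: some of these patients will lack videofluoroscopy, and the estimate will include non-adherence.

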### Intervention

The training protocol consists of IEMT and standard swallowing exercises. Patients will be instructed to maintain a rate of 15–20 breaths/min using the Orygen-Dual® valve (described elsewhere in detail) [21, 22], a respiratory device that allows patients to train inspiratory and expiratory muscles simultaneously. Training loads will be set at a pressure equivalent to 10 maximal repetitions (if tolerated). These external pressures will be regulated weekly at 30% of maximal inspiration/expiration respiratory measures obtained. Patients will be instructed to perform 3 sets of 5 repetitions and standard swallowing exercises (mobility and tonicity exercises of the tongue, palate, larynx, and constrictor muscles), 3 times/day, 5 days/week, for 21 weeks. An experienced swallowing therapist will supervise IEMT weekly. The protocol will be the same for both groups, but one group will start 2 weeks before CRT and the other one will begin immediately after completing CRT (Fig. 1).

### Outcome measures

Main outcome variable:
Change in dysphagia severity observed by VFSS and assessed with the Penetration-Aspiration Scale: scores 1–2 indicate normal swallowing, 3–5 penetration, and ≥ 6 aspiration

Secondary outcome variables:
Change in quality of life, assessed with the European Organization of Research and Treatment of Cancer (EORTC) Quality-of-Life Questionnaire (QLQ-C30) and its Head and Neck Cancer Module (QLQ-H&N35).Mouth opening or the maximal interincisor opening (MIO) of the mouth, using the Therabite® range of motion scale.Maximum isometric tongue pressure in an anterior position.Maximum inspiratory and expiratory pressures (PImax and PEmax, respectively).Impaired security (tone of voice, coughing during or after eating, or desaturation > 3% compared to baseline pulse oximetry) and efficacy in oral and pharyngeal phases of swallowing with the use of the Volume-Viscosity Swallow Test.Subjective difficulty of swallowing assessed by a Visual Analogic Scale (VAS) ranging from 0 to 10; a low score indicates no difficulties in eating and a high score, no oral intake.Peak cough flow (PCF) will be used to evaluate the effect of IEMT on voluntary cough. It is measured with spirometer in liters/minute. Patients will be instructed to perform three repetitions of voluntary cough and the best one will be chosen.

### Participant timeline

Eligible patients will be randomized and referred to the Rehabilitation Department for function assessment and intervention. The study outcomes will be assessed at baseline (2-week pre-CRT, t_0_), at the beginning of CRT (t_1_), at the end of CRT (t_3_), and thereafter at 3 months (t_4_), 6 months (t_5_), and 12 months (t_6_). The Redyor schedule of enrollment is shown in Fig. 2.

**Fig. 2 Fig2:**
[figure not shown]
SPIRIT diagram of the project stages for the Redyor study

### Sample size calculation

Accepting an alpha risk of 0.05 and a beta risk of 0.2 in a two-sided test, a total sample size of 52 patients will be required to detect a difference ≥ 10 (SD 11) units in the test of quality of life and 2 (SD 2.3) units in the PAS. In order to account for estimated 20% loss to follow-up, five patients have been added, resulting 26 patients on each group.

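### The sample-size paragraph gives 52 both as the number needed for 80% power and as the number after the allowance for loss; the stated inputs support only the second, with five added per group

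*Protocol article*

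**What the plan says.** The Sample size calculation section of the protocol article has two sentences. The first sets the error rates, "Accepting an alpha risk of 0.05 and a beta risk of 0.2 in a two-sided test", and states that "a total sample size of 52 patients will be required to detect a difference". The differences are "a difference ≥ 10 (SD 11) units in the test of quality of life" and "2 (SD 2.3) units in the PAS". The second sentence deals with loss: "In order to account for estimated 20% loss to follow-up, five patients have been added", which brings each group to 26.

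The section does not give the number before the addition. It does not say whether the five are per group or in total, and it names no formula. The Strengths and limitations section repeats that "sample size estimation assumed a loss of about 20% of patients". The Abstract also gives 52 patients.

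Two other sections matter. Outcome measures names PAS as the main outcome and lists quality of life as secondary. Statistical methods plans an independent-samples t-test on the changes and drops missing data.

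**The concern.** Two groups of 26 make 52, so the paragraph starts from 52, adds patients and arrives at 52. Either the first sentence gives the inflated total as though it were the requirement, or the second sentence adds nothing.

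The two readings lead a reader to different judgements. If 52 were needed for 80% power, a trial that ended with about 42 analysable patients would look ten short. If 52 is the number to randomise, about 42 analysable patients is what the design expected. In the same way, a reader who takes the five as a total would conclude that the allowance was about half of the 20% claimed.

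**Working it through.** **Inputs**, all from Sample size calculation: two-sided alpha 0.05 (z = 1.96); power 0.80 (z = 0.8416); PAS difference 2, SD 2.3; quality-of-life difference 10, SD 11; loss 20%; five added; 26 per group.

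**1. Evaluable patients needed per group.** Normal approximation: n = 2 × (1.96 + 0.8416)² / d², where d = difference / SD.

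- PAS: d = 2 / 2.3 = 0.8696, n = 20.76, so 21 per group and 42 in total. By t-test (noncentral t): 21.76, so 22 per group and 44 in total.
- Quality of life: d = 10 / 11 = 0.9091, n = 18.99, so 19 per group and 38 in total. By t-test: 20.00, which is 20 per group, or 21 if rounded up strictly (20.0016).

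**2. Reproducing 26 per group.** 21 + 5 = 26 per group and 52 in total. The allowance is 5 / 26 = 19.2%, which agrees with about 20%. Dividing by the retention rate gives 21 / 0.8 = 26.25, also about 26. So 52 is reproduced as the total after inflation, with ten added across the trial.

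**3. Testing the other readings.**

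- 52 as the evaluable requirement: the number to randomise would be 52 / 0.8 = 65, and adding five would give 57. The section gives neither.
- Five added in total: the base would be 52 − 5 = 47 and the allowance 5 / 52 = 9.6%, against the stated 20%. A base of 47 also does not split evenly.
- A one-sided test needs 17 per group for PAS, and 90% power needs 28 (both by normal approximation), so neither makes 26 the pre-loss number for PAS.
- By normal approximation, 26 per group before loss does come out for PAS at alpha 0.025, or for quality of life at 90% power. Both depart from the stated alpha or beta, and both leave nothing added for loss.

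**4. Power at the relevant sizes.** Normal approximation: power = Φ(d√(n/2) − 1.96). For PAS at 20.8 per group this is Φ(2.804 − 1.96) = Φ(0.844) = 0.801.

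| Per group | PAS, t-test | PAS, normal | QoL, t-test | QoL, normal |
|---|---|---|---|---|
| 26 (no loss) | 86.8% | 88.0% | 89.5% | 90.6% |
| 21 | 78.5% | 80.5% | 82.0% | 83.8% |
| 20.8 (26 less 20%) | 78.1% | 80.1% | 81.6% | 83.4% |

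The last row assumes that lost patients contribute nothing to the comparison. That follows from dropping missing data in a t-test.

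**The case against.** The strongest reply is that the design figure is right and only the prose is loose. The first sentence never calls the 52 evaluable. The second can be read as explaining how that total was reached, and because it ends by speaking of each group, five per group is a natural reading. Much of this stands. The number to randomise agrees with the inputs and with the Abstract. The missing words about the five are an ambiguity rather than a wrong sum.

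It does not clear the first sentence, which ties 52 directly to beta 0.2 as what is required. Under either formula 52 is not what those inputs require, and the number that is required appears nowhere.

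Three stronger conclusions are tempting, and the document supports none of them.

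- *The trial is underpowered at 78%.* That figure takes a size that matches the normal approximation and evaluates it with the t-test. The normal approximation returns 80.1% at the same size. The section does not say which formula was used, and the gap is about two points.
- *The two differences joined in one sentence promise power to show both effects.* Outcome measures names one main outcome, and nothing in the article claims that both must succeed. The sentence lists two sets of inputs.
- *Sixty-five patients should have been randomised.* That holds only if 52 is the evaluable requirement, which the inputs contradict.

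The listed end of recruitment (August 2018) also precedes publication (August 2019), so the wording changes no recruitment target.

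**Conclusion.** The point holds as a reporting error in the sample-size justification for the main outcome. As written, 52 is both the requirement for 80% power and the total after the allowance, and both cannot be true. The stated inputs need 42 (normal approximation) or 44 (t-test) evaluable patients for PAS, which is 8 to 10 fewer than the first sentence says. At the stated alpha and power, 52 makes sense only as the number to randomise, with five added per group.

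This rests on equal groups, on the stated SDs applying to the between-group comparison of changes, and on a base of 21 per group. That base is inferred from 26 − 5, because the article does not state it. It agrees with the normal approximation for PAS; the t-test base of 22 plus five would give 27.

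Severity is minor to moderate. The design, the main outcome and the analysis are unaffected, and any shortfall in PAS power depends on the formula and is about two points.

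**What to change.** Replace the paragraph with a statement along these lines, once the sponsor has confirmed which formula was used:

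> With a two-sided alpha of 0.05, 21 evaluable patients per group (42 in total) give about 80% power by normal approximation (about 79% by the planned t-test) to detect a 2-unit difference in PAS (SD 2.3), the main outcome. The same number gives about 82 to 84% power for a 10-unit difference in quality of life (SD 11). Five patients per group (ten in total) are added for about 20% loss, giving 26 per group and 52 to randomise.

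If the calculation was in fact a t-test with 22 per group, the text should say so. Reaching 26 then means four added per group, an allowance of 4 / 26 = 15.4%, and the stated 20% would have to be reconciled with that.

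The cost is rewording only. No more patients are needed and the analysis does not change. The one less favourable effect is that the t-test power for PAS is shown as slightly under 80%.

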#### Blinding

The interdisciplinary researchers ([name]) will be blinded to study group assignments over the entire study period. After data analysis has been completed, results will be released to all patients and to participating clinicians and researchers.

### Data collection, management, and analysis

#### Data collection methods

The main outcomes will be collected by means of a Data Collection Logbook specially designed for this study. This logbook will include the EAT-10 and both quality of life questionnaires (EORTC-QLQ-C30 and QLQ-H&N35). One member of the investigation team ([name]) shall be responsible for the collection and processing of data related to main outcome variables. To promote participant retention, patients will perform a weekly supervised session; any patient not attending these scheduled sessions will be contacted by telephone.

